# Effect of low-dose amitriptyline on reducing pain in clinical knee osteoarthritis compared to benztropine: study protocol of a randomised, double blind, placebo-controlled trial

**DOI:** 10.1186/s12891-021-04690-y

**Published:** 2021-09-27

**Keywords:** Knee osteoarthritis, Pain, Amitriptyline

## Abstract

**Background:**

Knee osteoarthritis is a major cause of pain and disability. Pain control is poor, with most patients remaining in moderate to severe pain. This may be because central causes of pain, a common contributor to knee pain, are not affected by current treatment strategies. Antidepressants, such as amitriptyline, have been used to treat chronic pain in other conditions. The aim of this randomised, double blind, controlled trial, is to determine whether low dose amitriptyline reduces pain in people with painful knee osteoarthritis over 3 months compared to benztropine, an active placebo.

**Methods/design:**

One hundred and sixty people with painful radiographic knee osteoarthritis will be recruited via clinicians, local and social media advertising. Participants will be randomly allocated in a 1:1 ratio to receive either low dose amitriptyline (25 mg) or active placebo (benztropine mesylate, 1 mg) for 3 months. The primary outcome is change from baseline in knee pain (WOMAC pain subscale) at 12 weeks. Secondary outcomes include change in function (total WOMAC) and the proportion of individuals achieving a substantial response (≥ 50% reduction in pain intensity, measured by Visual Analog Scale, VAS, from no pain to worst pain imaginable, 0-100 mm) and moderate response (≥ 30% reduction in pain intensity, measured by VAS) at 12 weeks. Intention to treat analyses will be performed. Subgroup analyses will be done.

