### Hypothesis and objectives

We aim to determine whether the use of low dose amitriptyline reduces pain in people with painful radiographic knee OA over 3 months compared to the use of benztropine, an active placebo. Our secondary objectives include determining whether amitriptyline improves knee function and results in a higher proportion of people achieving a clinically significant reduction in pain compared to those on placebo. We hypothesis that those taking low dose amitriptyline will have improved pain and function compared to those taking active placebo, and that the proportion achieving a clinically significant improvement will be higher in participants receiving amitriptyline compared to those on placebo.

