**ASSESSMENTS**					
**Primary and secondary outcomes**					
WOMAC (pain, stiffness, function, total)		x			x

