#### Secondary outcomes

Change in knee symptomatology between baseline and 12 weeks will be assessed using *change in total WOMAC* score (5 pain items, 2 stiffness items and 17 function items, each measured on a 100 mm VAS will be added and the results normalised to 1–100). A measure of knee overall function is recommended by OARSI.

*Pain severity, achieving a clinically significant response* assessed by percentage reduction in participant’s current level of knee pain, recorded on VAS, ranging from no pain to the worst pain imaginable (0 – 100 mm), from baseline to 12 weeks. The proportion attaining a substantial response (designated ≥ 50% reduction in pain intensity) and a moderate response (designated as a ≥ 30% reduction in pain intensity, as defined by the International Pain Society [24, 25].

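### The knee-function objective is tied to total WOMAC, which mixes in every primary pain item, so a function result can be inflated or diluted; the 17-item function subscale should be named instead

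*Protocol article*

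**What the plan says.** Under Hypothesis and objectives, the protocol article states: "Our secondary objectives include determining whether amitriptyline improves knee function". The hypothesis there is that "those taking low dose amitriptyline will have improved pain and function compared to those taking active placebo".

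The abstract (Methods/design) links this objective to an outcome: "Secondary outcomes include change in function (total WOMAC").

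Under Outcome measures, Secondary outcomes, the same score is introduced differently: "Change in knee symptomatology between baseline and 12 weeks will be assessed using" the change in total WOMAC. It is built as follows: "5 pain items, 2 stiffness items and 17 function items, each measured on a 100 mm VAS will be added" and then normalised. That paragraph ends by justifying the choice as a recommended measure of the knee's overall function. One score is therefore called function in the abstract and both symptoms and function in the methods.

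Under Primary outcome, the primary measure is the five-item WOMAC pain scale, also on 100 mm VAS items and normalised to 0–100. These are the same five items.

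Table 1 lists "WOMAC (pain, stiffness, function, total") at baseline and 12 weeks, in the block for primary and secondary outcomes. The Secondary outcomes text names only the total. ACR functional class and muscle strength are placed among the other measures, not the secondary outcomes.

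**The concern.** A secondary objective needs an outcome that answers it. The function question is answered by a score in which 7 of 24 items do not measure function, and 5 of those 7 are the primary outcome.

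This has two consequences. If pain improves more than function, the total overstates the function effect, and part of a positive function finding repeats the primary result. If function improves and pain does not, the total understates it. In neither case can a result on the total be attributed to function.

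The Statistical analysis section makes no adjustment for multiple testing. A significant total could therefore be read as separate support for a function benefit although it shares items with the primary outcome.

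**Working it through.** **Inputs.** Item counts 5, 2 and 17 (Secondary outcomes). Difference 10 mm, SD 20 mm, two-sided alpha 0.05, 64 per arm, pre-post correlation 0, 20% loss (Sample size, Primary outcome). The same 10 mm and SD 20 mm are given for total WOMAC (Sample size, Secondary outcomes). No SD is given for the function subscale, so 20 mm is assumed for it.

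**The plan's own figure.** n per arm = 2(1.96 + 0.842)² × 20²/10² = 62.8, so 63 by the normal formula and 63.8, so 64, by the t-test. Power at 64 per arm is 0.807 (normal) or 0.801 (t-test). Then 64/0.8 = 80 per arm, 160 in total. The figure reproduces.

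**Weights.** All items have the same range and are summed, so the normalised total is

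T = (5 × P + 2 × S + 17 × F)/24,

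where P, S and F are the pain, stiffness and function scores on 0–100. Pain carries 5/24 = 20.8%, stiffness 2/24 = 8.3%, function 17/24 = 70.8%, and non-function items together 7/24 = 29.2%. A between-arm difference in T is the same weighted mean of the three differences. A 10 mm difference on the total equals a 10 mm function effect only if the other items also move by 10 mm on weighted average.

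**Power.** The standard error of a difference is 20 × √(2/64) = 3.54 mm. Power is approximately Φ(difference/3.54 − 1.96), plus the opposite tail where it matters.

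| Illustrative true effect (mm) | Difference on total | Power on total | Power on function subscale (SD 20 assumed) |
|---|---|---|---|
| Pain 10, stiffness 0, function 0 | 50/24 = 2.1 | about 9% | 5% (null) |
| Pain 10, stiffness 5, function 5 | (50 + 10 + 85)/24 = 6.0 | about 40% | about 29% |
| Pain 0, stiffness 0, function 10 | 170/24 = 7.1 | about 52% | about 80% |

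**How far pain alone could go.** The smallest observed difference on the total with p < 0.05 is about 1.96 × 3.54 = 6.9 mm. Pain alone would need 6.9 × 24/5, about 33 mm, to reach it, and 10 × 24/5 = 48 mm to produce the planned 10 mm. With SD 15 to 20 mm and pre-post correlation 0 to 0.7 (assumed ranges), the chance that a 10 mm pain-only effect makes the total significant is 9% to 20%.

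**Dependence on the assumed SD.** For a function-only effect, the subscale has more power than the total as long as its SD is below 20 × 24/17 = 28.2 mm.

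**The case against.** The strongest defence is that total WOMAC is mostly function (17 of 24 items), that the methods disclose its content item by item, and that they already introduce it as a symptom score. On this view the abstract's parenthesis is only a loose summary. Table 1 also places the function subscale in the block for primary and secondary outcomes, and the Statistical analysis section gives a baseline-adjusted regression for continuous outcomes of that kind. An analysis of the subscale may therefore already be intended.

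Much of this stands. The composite is a defensible secondary outcome, its content is not hidden, and the subscale is not absent from the trial. What remains is that the Secondary outcomes text names no pure function measure and labels the total both ways. Table 1 and that text differ on which WOMAC scores count as secondary outcomes.

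A reader might go further and infer that a significant function result could come from pain alone. The plan's own figures do not support that. At the planned 10 mm, pain alone moves the total by only 2.1 mm, and it would take about 33 mm to reach significance.

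A second fair objection is cost. The article's Trial registration section records changes to the secondary outcomes in February and July 2021, so this would be a further late change.

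**Conclusion.** The concern holds as a matter of contamination and labelling. The outcome named for function contains the whole primary outcome, is about 71% function by weight, and is described inconsistently. At the planned pain effect the distortion is moderate: power of about 40% against 29% when pain adds to a 5 mm function effect, and about 52% against 80% when a 10 mm function effect stands alone. These contrasts use illustrative effects, 64 per arm, zero pre-post correlation and an assumed SD of 20 mm for the subscale.

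No sample size or power statement is shown to be wrong on this point, and the primary analysis is unaffected. The total's range, given as 1–100 under Secondary outcomes and 0–100 under Sample size, is a clerical slip and adds nothing to the argument.

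**What to change.** In the abstract and under Secondary outcomes, name change from baseline to 12 weeks in the WOMAC function subscale (17 items, normalised to 0–100) as the outcome that answers the function objective. Analyse it with the baseline-adjusted linear regression already planned for continuous outcomes. Keep total WOMAC as a secondary outcome and call it overall knee symptoms throughout. Correct its range to 0–100 at the same time.

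The data are already scheduled in Table 1, so nothing new is collected. If the subscale's SD is close to 20 mm, the sample size still gives about 80% power for 10 mm. The cost is one more secondary outcome without multiplicity adjustment and a further registry amendment, which should be dated and made before the allocation code is revealed.

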**Discussion:**

This study will provide high level evidence regarding the effectiveness of low dose amitriptyline compared to benztropine in reducing pain and improving function in knee OA. This trial has the potential to provide an effective new therapeutic approach for pain management in knee osteoarthritis, with the potential of ready translation into clinical practice, as it is repurposing an old drug, which is familiar to clinicians and with a well described safety record.

**Trial registration:**

Australian New Zealand Clinical Trials Registry prior to recruitment commencing (ACTRN12615000301561, March 31, 2015, amended 14 December 2018, February 2021). Additional amendment requested 18 July 2021.

## Background

Knee osteoarthritis (OA) is a major cause of pain and disability, estimated to affect 654 million people worldwide [1], with the lifetime risk estimated to be 44.7% in the USA [2]. Most people with OA (58%) live with moderate to severe chronic pain [3]. People with knee OA rank pain as their highest treatment priority [4], as it limits function, independence, quality of life and leads to costly joint replacement [5].

The management of knee OA aims to reduce pain, optimise function and reduce disease progression. OA management guidelines focus on patient education, weight management and exercise therapy [6], but even with excellent patient engagement, the effect sizes of these interventions are moderate at best [7]. Practically, pharmacological interventions are the mainstay of pain control. However, their effect is also limited. A recent Cochrane review concluded that paracetamol provides only minimal clinical benefit [8]. Although non-steroidal anti-inflammatory drugs (NSAIDs) provide a small to moderate effect on analgesia, they are associated with significant adverse effects, particularly in the elderly which limits their use [9]. Although opiates are used [6], with no proven long term benefit [10], there is evidence of significant harm [11]. As a result, over half (54%) of patients with knee OA report that their knee pain is not well controlled [12].

Pain control in OA may fail because treatment is not targeted to the cause of pain which is multifactorial. Although the severity of structural pathology is associated with the prevalence of pain, it does not explain the intensity of pain [13, 14], suggesting that factors outside the joint play a role. Pain sensitisation, is an abnormal state of responsiveness or increased gain in the reception of pain [15]. Pain sensitisation may play a role in some patients with OA, where a painful peripheral stimulus relating to the joint is amplified and augmented by changes in the spinal cord and central nervous system [15]. Clarifying whether this is the cause of pain in an individual is important, as response to therapy will be influenced by the cause of pain [16].

For pain related to sensitisation, the most commonly used analgesics in OA, paracetamol, COX2 inhibitors, NSAIDs and opioids may be ineffective [16]. For central causes of pain and sensitisation, antidepressants may be helpful. Duloxetine, a serotonin and norepinephrine reuptake inhibitor (SNRI) antidepressant, has been conditionally recommended for use by international OA guidelines for some people with OA, although which patients are not specified [6]. Low dose tricyclic antidepressants, are commonly used in chronic neuropathic pain states (eg diabetic peripheral neuropathy [17]) and central pain states (eg fibromyalgia [17]). They have not been fully trialled in OA [17]. Until recently, human studies of low dose tricyclic antidepressants for knee pain in OA have been limited to 2 small studies; although they showed improvement in knee pain they had no control population [18, 19]. There has only been a single recent controlled trial of nortriptyline, but not amitriptyline, in patients with painful clinical knee OA [20]: radiographic criteria were not used.

### Hypothesis and objectives

We aim to determine whether the use of low dose amitriptyline reduces pain in people with painful radiographic knee OA over 3 months compared to the use of benztropine, an active placebo. Our secondary objectives include determining whether amitriptyline improves knee function and results in a higher proportion of people achieving a clinically significant reduction in pain compared to those on placebo. We hypothesis that those taking low dose amitriptyline will have improved pain and function compared to those taking active placebo, and that the proportion achieving a clinically significant improvement will be higher in participants receiving amitriptyline compared to those on placebo.

## Methods

### Study design

The Knee Osteoarthritis Pain Study (KOPS) is a single centre, pragmatic, randomised, double blind, active placebo controlled clinical trial over 12 weeks.

### Trial registration

The trial was registered on the Australian New Zealand Clinical Trials Registry prior to recruitment commencing (ACTRN12615000301561, March 31, 2015, amended 14 December 2018, February 2021). Reporting will be in accordance with the Consolidated Standards of Reporting Trials (CONSORT) Statement [21]. Protocol reporting is in accordance with the SPIRIT Statement (Standard Protocol Items: Recommendations for Interventional Trials) [22]. In December 2018, the protocol was amended to include participants with severe radiographic knee OA (grade 3 according to OA Research Society International atlas) on the basis of pain sensitisation, the mechanism targeted by amitriptyline, being prevalent in approximately 30% of those with more severe disease [23]. The protocol was further amended in February 2021 to remove the OARSI responder criteria as a secondary outcome on the basis of uncollected data [24, 25], with replacement by the proportion achieving a substantial and moderate response, as defined by the Initiative on Methods, Measurement, and Pain Assessment in Clinical Trials (IMMPACT), in July 2021 [24].

### Ethics approval

Ethics approval has been obtained from the Alfred Hospital Ethics Committee (512/14) and registered with the Monash University Human Research and Ethics Committee (CF15/1488–2,015,000,729). Participants will only be included after they have provided informed consent.

### Study setting and participants

In a single site study, we aim to recruit 160 participants from the Victorian community with painful knee OA. Recruitment will use a combined strategy involving general practitioners, rheumatologists, orthopaedic surgeons, and advertising in local and social media.

### Eligibility criteria

#### Inclusion criteria

Male and female participants with painful knee OA (pain for ≥ 3 months), defined according to ACR clinical and radiographic criteria, with pain of > 30 mm on a 100 mm visual analogue scale (VAS) and age 40–75 years required.

#### Exclusion criteria

These include: 1) Inability to give informed consent; 2) Intra articular therapy over the past 3 months; planned injection or surgical intervention in the next 4 months 3) Rheumatoid or other inflammatory arthritis, or significant knee injury; 4) Major depressive disorder for which anti-depressant therapy is indicated 5) Taking medications that are contra-indicated when taking amitriptyline (monoamine oxidase inhibitors, other antidepressants, opioids, drugs that inhibit CYP3A4, etc) 6) Co-morbidity that may limit participation (eg. planned joint replacement in the next 4 months, medical conditions eg. malignancy in the past 5 years other than non-melanoma skin cancer) or relocation; 7) Fibromyalgia, as this may provide an alternative underlying explanatory condition 8) Contraindication to amitriptyline eg acute angle glaucoma, prostatism, etc. 9) Pregnancy or planned pregnancy. Severe radiographic knee OA (grade 3 according to OA Research Society International atlas) was initially a cause for exclusion, which was amended in the protocol in December 2018 as pain sensitisation, the mechanism targeted by amitriptyline, is prevalent in those with more severe disease [23].

### Participant timeline

Table 1 shows the assessments at each time point, according to the Standard Protocol Items: Recommendations for Interventional Trials (SPIRIT Statement). Figure 1 provides the flow of participants in the study.

**Table 1 Tab1:** Schedule of study flow and assessments

	Enrolment	Baseline	2 weeks	6 weeks	12 weeks
**ENROLMENT:**					
Eligibility screen	x				
Informed consent	x				
Clinical assessment		x			
Randomisation		x			
**INTERVENTION:**					
Amitriptyline, 25 mg nocte		Alternate	Nightly	Nightly	Nightly
Benztropine, 1 mg, nocte		Alternate	Nightly	Nightly	Nightly
**ASSESSMENTS**					
**Primary and secondary outcomes**					
WOMAC (pain, stiffness, function, total)		x			x
**Other measures of knee pain**					
Pain severity (NRS, 0–10)		x	x	x	x
Pain severity (VAS, 100 mm), pain diagram		x			x
PainDETECT		x			x
**Functional status and severity**					
ACR functional class I, II or III		x			x
Investigator assessed global assessment of OA status (Likert, 0 very well–4 very poor)		x			x
General health status (AQOL-8D)		x			x
Leg muscle strength (in triplicate)		x			x
Xray – KL score, osteophytes, JSN		x			
**Other measures of response**					
Pain acceptability (48 h)		x			x
Patient global impression of change (Likert, 0–7)			x	x	x
**Other measures**					
Inclusion criteria: pain & 1 of age > 50, stiff <30mins, Crepitus, osteophytes and KOA		x			
Age, height, weight, bp, smoking		x			
Medical conditions		x			x
Education (category), Employment current status, type of work (manual, office, NA)		x			
Medications – analgesics, NSAID, opioid		x			x
Fear of movement (TSK)		x			x
Mood disorder (HADS)		x			x
Physical activity (IPAQ, 7 days)		x			x
Sleep quality and disturbance (PSQI)		x			x
**Treatment and safety issues**					
Medications – analgesics, NSAID, opioid		x			x
Treatment belief: study drug or placebo					x
Rating of medication and side effects (Scale, excellent, good, fair, poor, unacceptable)					x
UKU		x	x	x	x
Adverse events			x	x	x
Adherence, pill count					x

*WOMAC* Western Ontario and McMaster Arthritis Index. *NRS* Numerical rating scale *VAS* visual analogue scale, *AQOL-8D* Assessment of quality of life. *TSK* Tampa Scale of Kinesiophobia *HADS* Hospital anxiety and depression scale *IPAQ* International physical activity questionnaire *PSQI* Pittsburgh sleep quality index UKU: UKU Side effect rating scale for psychotropic drugs

**Fig. 1 Fig1:**
[figure not shown]
Flow of participants

### Intervention

Participants will be randomised to treatment with capsules, identical in appearance, containing either 1) low-dose amitriptyline (Symbion, NSW), initially 25 mg on alternate days for the first 2 weeks, to improve compliance and reduce side effects, increased to 25 mg daily thereafter; or 2) benztropine, an active placebo, at a dose of 1 mg alternate days for the first 2 weeks, to improve compliance and reduce side effects, increased to 1 mg daily thereafter (Symbion, USA).

Amitriptyline was chosen, being the most effective tricyclic antidepressant for managing neuropathic pain and fibromyalgia, at a dose used in these conditions [17]. Benztropine, an active placebo, was chosen as it mimics the anti-cholinergic effects of amitriptyline (eg dry mouth, constipation), and is not known to effect pain. Benztropine will produce more effective blinding of study participants and investigators than an inert placebo. The reduction in potential for unblinding explains why benztropine has been used as an active placebo in previous trials [26].

### Randomisation, allocation concealment, double blinding and control of bias

Participants will be randomised in a 1:1 ratio, to amitriptyline or benztropine, according to a computer-generated randomisation sequence with permuted blocks of random sizes, held securely by the dispensing clinical trials pharmacy. This will be generated by a statistician, with no direct involvement in study execution. This process ensures that participant allocation cannot be accessed or influenced by research personnel.

The randomised controlled trial, will be double blind, with both participants and investigators assessing study outcomes blinded to treatment allocation. Allocation concealment and double blinding will be achieved by 1) dispensing by clinical trials pharmacy; 2) using an active placebo, identical in appearance to active study drug, with side effects that mimic those of amitriptyline with dose escalation; 3) subjective measures of study outcomes being taken by research assistants uninvolved in other aspects of the trial and unaware of group allocation; 4) data analysis will be completed prior to the allocation code being revealed.

Unblinding will be possible in the event of medical necessity, impacting on study participant safety. Code-break envelopes for the randomisation schedule will be held by Monash University. Should participants be unblinded, they will be withdrawn from the trial.

